## Abstract

**Background:**

The effectiveness of acupuncture for patients with chronic tension-type headache (CTTH) is controversial. In this article, we report the protocol for a randomized controlled trial aiming to evaluate the long-term effect of acupuncture for CTTH, in comparison with superficial acupuncture.

**Design:**

A two-armed, parallel-design, patient-assessor blind, randomized controlled trial is underway in China. A total of 218 participants with CTTH will be randomly assigned to the treatment group or the control group in a 1:1 ratio. Participants in the treatment group and control group will receive acupuncture or superficial acupuncture treatments in a fixed prescription of acupoints respectively, for a total of 20 sessions over 8 weeks. The posttreatment follow-up period will be 24 weeks. The primary outcome will be the proportion of responders assessed at week 16 after randomization. The secondary outcomes will include the number of headache days, the mean intensity of headache, the reduction of medication intake, results from the 36-item short form health survey, the Hamilton Depression Scale and the Hamilton Anxiety Scale, the number of participants with adverse events, the expectation value of acupuncture treatment, and the intensity of *deqi* sensation. The first five secondary outcomes will be assessed or calculated at baseline, and at 4, 8, 12, 16, 20, 24, 28, and 32 weeks after randomization. Moreover, the expectation value will be collected at baseline and at week 8 after randomization, the intensity of *deqi* sensation will be assessed at 5 minutes after each treatment and adverse events will be summarized at the end of the follow-up period.

**Discussion:**

Results from this trial will provide evidence for the long-term effect of acupuncture for CTTH with a long follow-up period.

**Trial registration:**

ClinicalTrial.gov NCT03133884. Registered on 25 April 2017.

**Electronic supplementary material:**

The online version of this article (doi:10.1186/s13063-017-2188-9) contains supplementary material, which is available to authorized users.

## Background

Chronic tension-type headache (CTTH) is a disorder evolving from frequent episodic tension-type headache (TTH), typically bilateral, pressing or tightening in quality, mild to moderate in intensity, lasting hours to days, or unremitting [1]. In April 2016, the World Health Organization reported that chronic headache, occurring on 15 or more days every month affected 1.7–4% of the world’s adult population, among which CTTH, as the most common chronic primary headache disorder, affected 1–3% of adults [2].

According to the guidelines developed by the European Federation of Neurological Societies, prophylactic treatment should be considered in patients with CTTH, and the recommended prophylactic drugs include amitriptyline, mirtazapine, venlafaxine, and muscle relaxants [3]. However, some unpleasant side effects of the recommended drugs have been reported, including sexual dysfunction, body weight changes, gastrointestinal discomfort, unusual bleeding, and bruising [4–6]. In addition to the serious adverse effects associated with the use of muscle relaxants, its evidence for application to CTTH patients is limited [7]. More importantly, issues such as medication overuse and how to prevent CTTH sufferers from developing medication overuse headache require greater attention.

Acupuncture, one of the most important components in traditional Chinese medicine (TCM), is widely used to relieve tension-type headache [3, 8]. Several trials of good quality have drawn the conclusion that acupuncture was superior to sham acupuncture in TTH treatment [9, 10]; some studies, however, have indicated no significant differences [11–13]. According to the National Institute for Health and Clinical Excellence clinical guidelines [8] and Cochrane Library systematic reviews [14, 15], acupuncture is recommended for CTTH management. Nevertheless, its scientific basis is still relatively limited owing to a lack of adequate statistical power, insufficient reports, or relevant methodological shortcomings in previous studies [16, 17].

CTTH is a chronic disorder characterized by persistent or recurrent attacks of headaches, thus the long-term effect of acupuncture is of particular importance because of its instant effect in treatments. Therefore, we have designed a randomized controlled trial (RCT) with a 36-week observation period to investigate and evaluate the long-term effect of acupuncture for CTTH.

## Method and design

### Study design

This study is a parallel-design, patient-assessor blind RCT comparing an acupuncture treatment group with a superficial acupuncture control group. Two hundred and eighteen patients with CTTH will be recruited through but not limited to: reviewing and screening of outpatients in the Teaching Hospital of Chengdu University of Traditional Chinese Medicine, university media releases, community advertisement including distributing leaflets via regular community health counselling, media campaigns, and network recruitment.

Eligible participants will be randomly assigned to the acupuncture treatment group or the superficial acupuncture control group with a 1:1 ratio. The total observation period will be 36 weeks, including a 4-week baseline period, an 8-week treatment period and a 24-week follow-up period. They will receive 20 sessions of acupuncture or superficial acupuncture treatment over 8 weeks (three sessions per week in the first 4 weeks and two sessions per week in the following 4 weeks). During the baseline, treatment and follow-up periods, participants will not be allowed to take any prophylactic medications (e.g., amitriptyline, clomipramine, and mirtazapine) for CTTH, but will be permitted to use necessary analgesics (e.g., ibuprofen, paracetamol and ibuprofen) when headache is unbearable The type, dose and time of administration will be recorded in headache diaries. Assessments will be conducted at baseline and at 4, 8, 12, 16, 20, 24, 28, 32, and 36 weeks after randomization. Figures 1 and 2 illustrate the time schedule of enrolment, interventions, assessments, and visits of participants. The reporting of this trial is conducted according to the Standard Protocol Items: Recommendations for Intervention Trials (SPIRIT) guidelines (Additional file 1).

**Fig. 1 Fig1:**
[figure not shown]
Flow chart of this trial

**Fig. 2 Fig2:**
[figure not shown]
SPIRIT figure of enrolment, interventions, and assessments using the 36-item short form health survey (SF-36), Hamilton Depression Scale (HAMD) and Hamilton Anxiety Scale (HAMA). *Deqi* sensation will be assessed at 5 min after each treatment

The Consolidated Standards of Reporting Trials [18] and the Standards for Reporting Interventions in Clinical Trials of Acupuncture [19] have been used as frameworks of methodology for designing this protocol.

### Participants

#### Study population and sample size

We will recruit CTTH sufferers who meet the diagnostic criteria in the International Classification of Headache Disorders, 3rd Edition (ICHD-3) formulated by the International Headache Society [1]. According to a previous study [11], the proportion of responders (at least 50% reduction in days with headache) was 46% after acupuncture treatment versus 35% after superficial acupuncture (odds ratio, 1.32). In this study, we expect an odds ratio of 1.35 when acupuncture is compared with superficial acupuncture. Assuming a significance level of 0.05, a study power of 0.8, and a correlation of 0.5 between independent variables (including study groups, assessment intervals, and the number of headache days at baseline), 199 participants are required to reject the hypothesis that acupuncture is equivalent to superficial acupuncture. Taking a 10% attrition bias into consideration, we will recruit 218 participants in total, with 109 in each group.

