#### Primary outcome

The primary outcome measurement is the proportion of responders at week 16. A responder is defined as a participant with a decrease of at least 50% less headache days during 4 weeks. A participant with a reduction of less than 50% headache days, including anyone with missing data, is defined as a nonresponder. This outcome measurement will be assessed at week 16 after randomization.

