### Statistical analysis

Primary analysis will be based on intention-to-treat population, including participants with at least one assessment of the primary outcome and one acupuncture session. Per protocol (PP) analysis will be performed to test the robustness of the primary analysis. PP population will include participants receiving at least 12 sessions of acupuncture and be assessed at week 8 and 16.

The primary outcome will be analyzed with a random intercept logistic regression model, taking treatment allocation as a random factor and taking sex, age, and duration of headache as fixed factors. The secondary outcomes (headache days, headache intensity, SF-36, HAMA, HAMD results) will be analyzed using a generalized least squares regression model, with the same covariates as the primary outcome. For the rest of outcomes, we will make pairwise comparisons using a general linear model adjusted for baseline value, age, sex, and disease course. Missing values of the primary outcome will be imputed by the last-observation-carried-forward method. We will run several sensitivity analysis to ensure the robustness of the imputation: first, lost-to-follow-up participants in the acupuncture group will be recognized as nonresponders, whereas those in the superficial acupuncture group will be recognized as responders; second, lost-to-follow-up participants will be counted as responders in the acupuncture group but nonresponders in the superficial group; Third, all lost-to-follow-up participants will be treated as nonresponders. Missing values in the secondary outcomes will be imputed by using the multiple imputation method (*n* = 5).

All confidence intervals will be two-sided 95% intervals comparing acupuncture to superficial acupuncture and all statistical hypotheses will be two-sided tests. Analyses will be performed using the R and Stata programs.

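### The responder rates 46% v 35% give an odds ratio of 1.58, not 1.32, and 199 participants do not give 80% power for the stated odds ratio of 1.35 at week 16

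*Protocol article*

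**What the plan says.** The section on study population and sample size takes its starting point from an earlier trial, with responder proportions of "46% after acupuncture treatment versus 35% after superficial acupuncture (odds ratio, 1.32". It continues: "we expect an odds ratio of 1.35 when acupuncture is compared with superficial acupuncture". The error rates follow: "Assuming a significance level of 0.05, a study power of 0.8". A further input is "a correlation of 0.5 between independent variables (including study groups, assessment intervals, and the number of headache days at baseline"; the article does not say how it enters the calculation. The result is that "199 participants are required to reject the hypothesis that acupuncture is equivalent to superficial acupuncture". An allowance of 10% for attrition takes this to 218, or 109 per group.

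Two other sections fix what is being powered. Under Primary outcome: "The primary outcome measurement is the proportion of responders at week 16". Under Statistical analysis: "all statistical hypotheses will be two-sided tests".

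**The concern.** Two things do not fit. First, an odds ratio of 1.32 is too small for 46% against 35%, so the effect measure and the percentages printed beside it disagree. Second, an odds ratio of 1.35 on a binary endpoint at one visit is a small effect, and about 100 participants per arm is far too few to detect it with 80% power.

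The Background justifies the trial partly by the inadequate power of earlier studies. If the 80% is not real, a non-significant result could be read as a properly powered negative finding when the design would usually have missed the effect it was planned on.

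**Working it through.** **Inputs.** Rates 46% and 35%, odds ratio 1.35, alpha 0.05, power 0.80 and total 199 come from the sample-size section. Two-sided testing is from Statistical analysis, the single week-16 proportion from Primary outcome, and 1:1 allocation from Study design. No control rate is stated for this trial; 35% is assumed from the cited study and varied below.

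**1. Effect measure**
- Odds ratio: (0.46/0.54)/(0.35/0.65) = 0.8519/0.5385 = 1.58.
- Rounding range: 45.5% v 35.5% gives 1.52, and 46.5% v 34.5% gives 1.65. So 1.32 is not the crude odds ratio.
- Risk ratio: 0.46/0.35 = 1.31, with a rounding range of 1.28 to 1.35. This is compatible with 1.32.

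**2. Trying to reproduce 199**

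An odds ratio of 1.35 from 35% gives p = (1.35 × 0.35)/(0.65 + 1.35 × 0.35) = 0.4725/1.1225 = 0.4209.

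Pooled two-proportion formula, with mean proportion 0.3855:

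n per arm = [1.96 √(2 × 0.3855 × 0.6145) + 0.8416 √(0.35 × 0.65 + 0.4209 × 0.5791)]² / 0.0709² ≈ 738, so 1,476 in total. The stated figure is 199.

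One exact match exists: 35% v 47.25% (1.35 read as a risk ratio) at one-sided 5% needs 199 per arm. It cannot be confirmed as the origin, and it contradicts both 199 as a total and the two-sided tests.

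**3. Power with 199 in total (99.5 per arm)**

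For an odds ratio of 1.35, the standard error is 0.0690 under the null and 0.0688 under the alternative. Then z = (0.0709 − 1.96 × 0.0690)/0.0688 = −0.93, which is 17.5% power.

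| Effect | Power, N = 199 | Total N for 80% |
|---|---|---|
| Odds ratio 1.35 (42.1% v 35%) | 17.5% | 1,476 |
| Risk ratio 1.35 (47.25% v 35%) | 41.9% | 506 |
| 46% v 35% | 35.1% | 624 |

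With 199, power reaches 80% only at about 54.6% v 35% (odds ratio 2.24). A one-sided test of the odds ratio 1.35 would have 26.8% power.

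**4. Control rate.** Two-sided power for an odds ratio of 1.35 is 9.9% at a control rate of 10%, 14.0% at 20%, 16.7% at 30%, 18.2% at 50% and 17.2% at 60%.

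**5. Correlation of 0.5, odds ratio 1.35**
- As collinearity it inflates the variance. Power falls to 14.2% (R² = 0.25) or 10.8% (R² = 0.5).
- As baseline adjustment at one visit (variance factor 1 − 0.25), power is 21.9%.
- As the mean of 8 visits, factor (1 + 7 × 0.5)/8 = 0.5625, power is 27.7%.
- As the mean of 8 visits with baseline adjustment, factor 0.5625 − 0.25 = 0.3125, power is 45.2% and N = 1,476 × 0.3125 = 461.

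On that last reading the larger effects do pass 80%: 46% v 35% has 81% power (N = 624 × 0.3125 = 195), and 47.25% v 35% has 88% (N = 506 × 0.3125 = 158).

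**6. What 218 delivers at week 16 (109 per arm, control 35%)**

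The right-hand column multiplies each rate by 0.9, so that 10% drop out and count as nonresponders. For example, 47.25% v 35% becomes 42.5% v 31.5%.

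| | No dropout | 10% dropout as nonresponse |
|---|---|---|
| Power, odds ratio 1.35 | 19% | 17% |
| Power, 47.25% v 35% | 45% | 39% |
| Rate v 35% giving 80% power | 53.8% (odds ratio 2.16) | 55.6% before dilution |

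**The case against.** The strongest defence is that the calculation was longitudinal. The list attached to the correlation includes assessment intervals and baseline headache days, and the planned primary model is a random intercept logistic regression. On such a reading the correlation reduces the required number. With 8 visits and baseline adjustment, 46% v 35% needs about 195 participants, close to 199. A reader might infer that the correlation could only raise the sample size, or that no reading of it comes near the stated figure. Neither inference is supported, because the term is unexplained and the article condenses a fuller protocol. The 28% from averaging without baseline adjustment is not a ceiling either.

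This defence does not restore the claim. It reaches 80% only for effects larger than the stated odds ratio of 1.35, for which it gives about 45%. It also powers an average over visits, whereas the endpoint is one proportion at week 16. The approximation is itself rough for a binary outcome.

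A second tempting reading is that 1.32 and 1.35 are simply mislabelled risk ratios. The value 1.32 fits within rounding, but an adjusted odds ratio in the cited study cannot be excluded, and nothing in the article shows that 1.35 was meant as a risk ratio.

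It is also fair to say that 18% rests on an assumed control rate. That stands, but no rate from 10% to 60% raises the power above about 18%.

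**Conclusion.** The point holds in two parts. The percentages and the stated odds ratio contradict each other (1.58 against 1.32), and this needs no assumption. The stated 199 does not follow from the stated inputs for the week-16 endpoint. Power for an odds ratio of 1.35 is about 18% rather than 80%, and about 1,476 participants would be needed, more than seven times the plan. That second part rests on a 35% control rate, two-sided 5% testing, a simple two-proportion comparison and 199 as a total. Neither a different control rate nor a risk-ratio reading of 1.35 brings week-16 power near 80%.

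Where 199 came from, and whether the quoted ratios are risk ratios, cannot be settled from the article.

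**What to change.** Revise the sample-size paragraph as follows.

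- Reconcile 46% v 35% with the effect measure. Say whether 1.32 and 1.35 are odds ratios or risk ratios, and state the control rate assumed for this trial.
- State what the correlation of 0.5 does in the calculation, and drop it if it does not apply to an endpoint at one visit.
- Replace the 80% claim with what 218 participants deliver at week 16 at the assumed 35% control rate. With no dropout: about 19% for an odds ratio of 1.35, about 45% for 47.25% v 35%, and 80% only for about 53.8% v 35%. With 10% dropout counted as nonresponse, as the Primary outcome section defines missing data: about 17%, about 39%, and 80% only for about 55.6% v 35% before dilution.
- State that a non-significant result does not rule out the planned effect and will be interpreted from the confidence interval.

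The cost is a less favourable stated power. No extra patients are needed.

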### Randomization, allocation concealment and blinding

The Brightech Clinical Information Management System (CIMS) will be used for central randomization, which is performed by Brightech Clinical Medicine Research Co. Ltd. in Chengdu, China. Only authorized research assistants can obtain random numbers and group assignment information by logging into the CIMS website, which can ensure the randomization will not be influenced by researchers and patients. The randomization information will be concealed in the server until the end of the trial.

It is not possible to blind acupuncturists in this trial, therefore, they will not take part in the assessment procedure. Participants in different groups will receive treatment in different therapeutic rooms and be blinded to their treatment allocations. After all the treatment sessions, they will be asked to guess what kind of acupuncture treatment they have received (acupuncture or superficial acupuncture). Outcome assessors and statisticians will be blinded to the treatment allocation.

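### The sample size assumes a 0.5 correlation among predictors that include the randomised group and the assessment interval; this does not fit the single week-16 responder endpoint, and 199 does not follow from the stated inputs.

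*Protocol article*

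**What the plan says.** Under *Study population and sample size*, the protocol article cites an earlier study in which the responder proportion "was 46% after acupuncture treatment versus 35% after superficial acupuncture (odds ratio, 1.32", and it expects an odds ratio of 1.35 in this trial. It continues: "Assuming a significance level of 0.05, a study power of 0.8", and then "a correlation of 0.5 between independent variables (including study groups, assessment intervals, and the number of headache days at baseline". From these it derives 199 participants in total, raised to 218 (109 per arm) for 10% attrition.

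Three other sections bear on that sentence.

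- *Randomization, allocation concealment and blinding*: a central system "will be used for central randomization". *Study design* gives a 1:1 ratio and one assessment schedule for all participants.
- *Primary outcome*: the endpoint is the proportion of responders, and "This outcome measurement will be assessed at week 16 after randomization".
- *Statistical analysis*: the primary outcome is analysed by a random-intercept logistic model, "taking sex, age, and duration of headache as fixed factors". The same section says that "all statistical hypotheses will be two-sided tests".

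**The concern.** The 0.5 is described as a correlation among predictors, and one of those predictors is the randomised group. Randomisation makes group independent of every baseline variable in expectation. A shared visit calendar makes group unrelated to assessment interval, apart from the effect of dropout. So 0.5 is not a value that this design would be expected to produce.

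The inputs also describe a different analysis from the one planned. Assessment interval can be a predictor only where each participant contributes several outcome values, but the primary endpoint is one binary value at one time. Two of the three variables named in the sizing (interval and baseline headache days) are absent from the primary model's covariate list.

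The claim of 80% power is at stake. If it does not belong to the week-16 comparison, a non-significant result could be taken as adequately powered evidence of no difference. The article's *Background* criticises earlier trials for inadequate power.

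**Working it through.** **Inputs.** From *Study population and sample size*: alpha 0.05, power 0.80, odds ratio (OR) 1.35, reference rates 46% and 35%, correlation 0.5, N = 199. From *Statistical analysis*: two-sided tests. From *Study design*: 1:1 allocation. The 35% control rate is carried over from the cited study; the article does not say which control rate it used.

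**Step 1: is 0.5 plausible between group and baseline?** The expected value is 0. The chance SD with 199 participants is about 1/√198 = 0.071, and 0.5/0.071 ≈ 7.0. So 0.5 lies about 7 SDs from what randomisation gives.

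**Step 2: try to reproduce 199 for one week-16 comparison.** Per-arm formula, pooled variance, no continuity correction:

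n = [1.960·√(2p̄(1−p̄)) + 0.842·√(p₁(1−p₁) + p₂(1−p₂))]² / (p₂−p₁)²

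- OR 1.35 from 35%: odds 0.35/0.65 × 1.35 = 0.727, so p₂ = 0.727/1.727 = 42.1%. With difference 0.0709 and p̄ = 0.385, n = 738 per arm, **1,476** in total.
- 1.35 read as a risk ratio: p₂ = 0.35 × 1.35 = 47.25%. With difference 0.1225 and p̄ = 0.411, n = 253 per arm, **506** in total.
- 46% versus 35%: with difference 0.11 and p̄ = 0.405, n = 312 per arm, **624** in total.

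None of these is 199.

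**Step 3: put the 0.5 in.**

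- As written, a correlation of group with other predictors inflates the variance by 1/(1−0.5²) = 1.333. For OR 1.35 the total becomes 1,476 × 1.333 = 1,968, which is further from 199.
- As a within-participant correlation over m averaged assessments, the factor is (1+(m−1)·0.5)/m. For m = 8 it is 0.5625, giving about 830 (OR 1.35), 285 (risk ratio) or 351 (46% versus 35%). As m grows the factor falls only to 0.5, giving floors of 738, 253 and 312.
- As a baseline-adjusted average over eight assessments, the factor is 0.5625 − 0.25 = 0.3125. For 46% versus 35% this gives 624 × 0.3125 = 195, near 199. For the stated OR of 1.35 it gives 1,476 × 0.3125 ≈ 461.

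The 195 came from a wide search over variants. It uses rates implying a different OR from the one stated, and an average over visits instead of one week-16 value. It does not show how 199 was obtained.

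**Step 4: power at the planned size, one week-16 comparison.**

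| Effect | Total for 80% | Power, 199 evaluable | Power, 218 evaluable |
|---|---|---|---|
| OR 1.35 (35% vs 42.1%) | 1,476 | 18% | 19% |
| Risk ratio 1.35 (35% vs 47.25%) | 506 | 42% | 45% |
| 46% vs 35% | 624 | 35% | 38% |

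**Step 5: sensitivity to the control rate.** For OR 1.35 the total stays between 1,406 and 2,004 for control rates of 20% to 60%. Under the risk-ratio reading it depends strongly on that rate: 1,150 at 20%, 248 at 50%, 146 at 60%. A total of 199 would then need a control rate between 50% and 60%, well above the 35% cited.

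**The case against.** The best defence is that the sentence is mislabelled and that the authors had a repeated-measures analysis in mind. *Statistical analysis* specifies a random intercept, which normally presupposes several observations per participant or some other clustering. It also admits participants with at least one primary-outcome assessment, carries the last observation forward, and requires week-8 and week-16 assessments for the per-protocol set. On that view 0.5 is a within-participant correlation, or one between baseline and follow-up, and assessment interval belongs in the sizing.

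This stands in part. It makes a repeated-measures intention plausible, so it would be too strong to say that the planned model plainly lacks such a structure. But it moves the conflict without removing it. *Primary outcome* fixes one week-16 value, which cannot take the precision of averaged visits, and simple averaging with OR 1.35 does not come near 199.

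Three stronger readings might be inferred, and the documents support none of them.

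- That the 0.5 by itself explains the small sample. Taken literally it raises N, so it cannot. The effect-size label also contributes: 46% versus 35% is an OR of (0.46/0.54)/(0.35/0.65) = 1.58 and a risk ratio of 1.31, so 1.32 and 1.35 look like risk ratios called odds ratios.
- That deleting the 0.5 would shrink the 199 and leave the trial oversized. This treats 199 as valid output of the stated inputs, which it is not.
- That a group-baseline correlation of 0.5 is impossible. It is zero in expectation, not in every sample, so the accurate word is implausible.

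**Conclusion.** The concern holds as a mis-specified assumption. The stated correlation is incompatible with what randomisation and a common schedule would produce, the sizing includes assessment intervals that the week-16 endpoint cannot use, and 199 was not reproduced from the stated inputs under the article's own wording or under simple averaging of repeated assessments.

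For the endpoint as defined, "a study power of 0.8" is not delivered: 199 evaluable gives about 18% to 42% across the three effect readings, and 218 evaluable about 19% to 45%. These figures assume a 35% control rate, an unadjusted two-sided comparison of two proportions, and every counted participant having a usable week-16 value. The OR 1.35 result is robust to the control rate; the risk-ratio result is not. The share of the shortfall due to the correlation, as opposed to the effect-size label, cannot be separated until the sponsor discloses the method.

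**What to change.** 1. State which correlation the 0.5 represents and which method or software routine produced 199. Do this before removing anything, so that the basis of the original number stays on record.
2. Replace the calculation with one for the two-arm week-16 responder comparison: group independent of baseline, both assumed response rates given, and the effect measure named correctly. Any adjustment for baseline headache days can be described as a possible gain in precision.
3. Reconcile the random-intercept model in *Statistical analysis* with the single endpoint in *Primary outcome*. Either describe the repeated responder values that the model uses and the week-16 contrast taken from it, or describe a model for one value per participant.
4. Restate the power that 218 recruited participants give, allowing for the expected attrition.

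The cost is a rewritten sample size paragraph, a clarified model sentence, and a power figure that will probably be less favourable. Recruitment is under way and no additional participants are asked for.

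### The recruitment target of 218 does not quite cover the stated 10% attrition: it leaves about 196 participants with observed week-16 outcomes, against the 199 the plan requires

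*Protocol article*

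**What the plan says.** All the figures stand in the protocol article under Study population and sample size.

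- Required number: "199 participants are required to reject the hypothesis that acupuncture is equivalent to superficial acupuncture".
- Allowance for loss and resulting target: "Taking a 10% attrition bias into consideration, we will recruit 218 participants in total, with 109 in each group".
- Basis of the requirement: "Assuming a significance level of 0.05, a study power of 0.8, and a correlation of 0.5 between independent variables".

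Study design confirms equal allocation, so the total should be even. The article does not give the inflation formula. It also does not say whether the 10% is a share of those recruited or a margin added to 199. No other section states a different attrition rate or a different evaluable target.

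Two other sections affect what attrition means here. Primary outcome counts a participant with missing data as a nonresponder. Statistical analysis instead imputes missing primary outcomes by last observation carried forward. It limits the intention-to-treat population to participants with at least one primary-outcome assessment and one treatment session.

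**The concern.** An attrition allowance exists so that the required number remains after the expected loss. Attrition is normally a proportion of the people enrolled, so the required number n should be divided by (1 − d), where d is the expected loss. Multiplying by (1 + d) gives a smaller figure that falls short when the loss occurs. The stated 218 looks like the second calculation, truncated.

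What is at stake is whether the sample-size statement can be checked, more than the power of the trial. Readers will recompute it, and as written it says that 10% attrition is covered when it is not. The Discussion also accepts that the long observation period may increase dropout, so the allowance is likely to be used.

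**Working it through.** **Inputs** (protocol article, Study population and sample size): required n = 199 in total; attrition d = 10%; recruited N = 218, or 109 per arm; power 0.80 at significance level 0.05. Statistical analysis makes the tests two-sided: "all statistical hypotheses will be two-sided tests".

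**1. Reproducing the plan's figure.**
n × (1 + d) = 199 × 1.10 = 218.9. Rounded down, this is 218, the stated target. The other usual formula, in step 3, does not give 218. That multiplication was used is therefore inferred from the result.

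**2. What 218 leaves after a 10% loss.**
N × (1 − d) = 218 × 0.90 = 196.2, about 196, or 109 × 0.90 = 98.1 per arm. The shortfall against 199 is about 3.

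**3. What 199 would need.**
n/(1 − d) = 199/0.90 = 221.1, rounded up to an even 222 (111 per arm). Check: 222 × 0.90 = 199.8. The stated target is 222 − 218 = 4 lower, and 4/222 = 1.8%.

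**4. The loss that 218 can absorb.**
(218 − 199)/218 = 19/218 = 8.7%.

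**5. Is it only a matter of convention?**
If the 10% is a margin on 199, the figure is 218.9. A minimum is rounded up, to 219, or 220 for equal arms. Working back, 218/1.10 = 198.2, still below 199, but by less than one participant.

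**6. Effect on power, taking 80% at 199 as given.**
The standardised effect scales with the square root of the sample size. With two-sided 5% and 80% power it is 1.960 + 0.842 = 2.802 at 199.
At 196: 2.802 × √(196/199) − 1.960 = 2.802 × 0.9924 − 1.960 = 0.820, and Φ(0.820) = 79.4%.
The loss is about 0.6 percentage points.

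**7. Whether 199 can serve as the benchmark.**
Step 6 depends on 199 giving 80% power, and that was not reproduced as a two-sided total. The plan cites "46% after acupuncture treatment versus 35% after superficial acupuncture (odds ratio, 1.32" and designs for an odds ratio of 1.35. A standard two-proportion calculation (two-sided 5%, 80% power) gives 312 per arm, 624 in total, for 46% against 35%. For an odds ratio of 1.35 on a 35% control rate it gives 738 per arm, 1,476 in total. The article appears to rely on a model with correlated predictors, so these figures are not its own method. They show only that the 79.4% in step 6 is conditional.

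**The case against.** Four points can be made for the plan.

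**The formula is not written down.** A reader might infer that the protocol says it multiplied by 1.1. It does not. If the 10% was meant as a margin on 199, what remains is a rounding loss of under one participant. This stands as a limit on how the error is described. Even so, 218 falls below the requirement on both readings, and attrition is most naturally read as a share of those recruited.

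**Lost participants may still be analysed.** A reader might infer that only 196 people will enter the primary analysis. The documents do not support that. Under the nonresponder rule, people with missing data stay in the denominator. Under last observation carried forward, someone with an earlier assessment can also be kept. With a 10% loss, the number analysed could lie anywhere from about 196 to 218. This objection largely stands, and it is why 196 is described here as the number with observed week-16 outcomes. It does not make the allowance correct. The plan itself treats attrition as a loss that needs extra recruitment, and an imputed outcome carries less information than an observed one. Because the primary outcome is set at week 16, a literal reading of the intention-to-treat definition would also drop those lost before then.

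**The effect is negligible.** This stands. A gap of 4 in 222, or about 0.6 points of power, changes no design feature, analysis or conclusion.

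**The benchmark is itself doubtful.** This stands too. A power figure for 196 means nothing unless 199 is accepted, and any recalculation of 199 would replace this sentence.

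**Conclusion.** The sample-size statement is wrong as written, by a small amount. The figures 199, 10% and 218 are inconsistent: 218 with a 10% loss leaves about 196 observed outcomes, and it protects 199 only up to 8.7% attrition. This rests on reading attrition as a proportion of those recruited. On the other reading the shortfall is under one participant.

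The size is about 3 participants after loss, or 4 at recruitment. That is about 0.6 points of power, conditional on 199 giving 80%.

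Two stronger conclusions are tempting and should not be drawn. One is that the trial is materially underpowered because of this step: the arithmetic shows a trivial effect. The other is that moving to 222 would secure 80% power. That would require 199 to be sound, which is a separate and larger question that this correction does not settle.

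**What to change.** Keep 218 and correct the sentence under Study population and sample size. Either wording would do:

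- 218 recruited allows for 8.7% attrition while keeping 199 with observed week-16 outcomes; or
- 218 recruited with 10% attrition leaves about 196 (98 per arm) with observed week-16 outcomes.

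Add a clause saying that the number analysed may be higher, because missing primary outcomes are classed as nonresponse or imputed. Do not attach a power figure to 196 until the basis of 199 has been resolved. If the sample size is recalculated, inflate by n/(1 − d) and round up to an even total.

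The cost is one corrected sentence. It needs no extra enrolment and no change to procedures, and it can be made with recruitment under way.
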